**Discussion:**

The REMICRUSH trial protocol has been approved by the ethics committee of The Comité de Protection des Personnes Sud-Ouest et Outre-Mer II and will be carried out according to the principles of the Declaration of Helsinki and the Good Clinical Practice guidelines. The results of this study will be disseminated through presentations at scientific conferences and publications in peer-reviewed journals. The REMICRUSH trial is the first randomized controlled trial powered to investigate whether remifentanil with hypnotics is non-inferior to rapid-onset paralytic agents with hypnotic in rapid sequence induction of anesthesia for full stomach patients considering successful tracheal intubation without major complication.

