### Study endpoints

The primary endpoint is the proportion of patients with successful tracheal intubation without any significant complications up to 10 min after induction of anesthesia. Major complications during the first 10 min after induction of anesthesia are defined as the failure of tracheal intubation at the first attempt, pulmonary aspiration of gastric contents, oxygen desaturation < 95%, severe hemodynamic instability (mean arterial pressure (MAP) ≤ 50 mmHg or ≥ 110 mmHg for more than 3 min), severe arrhythmia (i.e., requiring pharmacological or electrical intervention or lasting more than 30 s), ventricular fibrillation or cardiac arrest, and anaphylactic reaction grade III or IV in HAS classification.

Secondary endpoints which will be compared between the two study groups are as follows:

In the operating theater: median intubation quality score (IDS-3 score) values [17], Cormack-Lehane (Supplemental Figure S1) and median POGO score values [18], percentage of patients requiring tracheal intubation alternative technique, median time between the administration of the hypnotic (start of anesthetic induction) and tracheal intubation (defined as the 6th capnography curve), median minimal value of SpO_2_ value within the first 10 min after anesthesia induction, percentage of patients with moderate desaturation (SpO_2_ ≤ 95%) or severe (SpO_2_ < 80%) within the first 10 min after anesthesia induction, percentage of patients with a severe hemodynamic disorder within the first 10 min after anesthesia induction (heart rate lower than 45 beats per minute (bpm) and/or higher than 110 bpm and/or a systolic blood pressure (SBP) lower than 80 mmHg and/or a SBP higher than 160 mmHg and/or a MAP of less than 55 mmHg and/or a MAP higher than 100 mmHg), frequency of patient with dental or tracheal injury during general anesthesia, frequency of patients with an allergic event of HAS 2013 grade I or II during general anesthesia, and the median doses of vasopressors used after induction,

In the recovery room: postoperative Sore Throat Score median values [19], percentage of patients with nausea, vomiting, aspiration of gastric contents, percentage of patients with laryngeal dyspnea, percentage of patients with SpO_2_ ≤ 92, percentage of patients with SpO_2_ < 80%, percentage of patients requiring post-extubation respiratory support, proportion of reintubation, and proportion of postoperative emergency ICU admission.

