After discharge of the recovery room: percentage of patients with postoperative pneumonia diagnosed up to day 7 and defined by the presence of new or progressive infiltrate on chest X-ray or C.T. scan, associated with any of the following symptoms: onset of purulent sputum, change in the appearance of chronic sputum, fever ≥ 38 °C, hyperleukocytosis (> 12,000/mL) or leukopenia (< 4000/mL), positive blood cultures or isolation of the pathogen on sputum, tracheal aspiration or bronchoalveolar lavage, percentage of patients with acute respiratory failure occurring up to day 7 defined by the combination of a clinical picture of acute hypoxemic respiratory failure, a PaO_2_/FiO_2_ ratio < 300 mmHg, the presence of new bilateral pulmonary infiltrates on the chest X-ray and the absence of evidence of cardiac origin, intra-hospital mortality up to day 7, and survival proportion at day 7.

Proportion of adverse events will be compared between the study groups. All expected and unexpected serious adverse events, as defined as EMA grade 3 (severe), 4 (life-threatening), to 5 (lethal), will be systemically recorded on day 1 and day 7. The proportion of expected and unexpected serious adverse events will be analyzed and reported in future publications.

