### Study oversight

Study sponsor is the Nantes University Hospital ([name], [contact]). Experienced research staff monitored the study for quality the integrity of data in all the participating centers. Serious adverse events and unexpected related or possibly related severe events are reported to the sponsor within 7 days.

The sponsor appoints an independent data and safety monitoring board (DSMB). The DSMB is composed up of 3 people with no connection to the research, including one co-author of the French Guidelines on muscle relaxants and reversal in anesthesia [20], one pharmacovigilance specialist, and one methodologist/biostatistician. Every 400 inclusions, the DSMB reviews safety issues as the study progresses. The DSMB makes recommendations to the sponsor about the continuation, modification, or termination of the research. The recommendations that the DSMB can make are:
To continue the research with no modificationsTo continue the research with a modification to the protocol or the monitoring of subjectsTo temporarily halt inclusionsTo permanently terminate the research in light of severe adverse reactions.

The sponsor can stop trial recruitment on the advice of the DSMB in case of safety concerns.

The Scientific Committee, composed of [name] (M.D.), [name] (M.D, Ph.D.), and [name] (Ph.D) approves the main study protocol and any amendments to monitor and supervise the trial concerning its primary and secondary objectives, to review relevant information from additional sources, to consider the recommendations of the DSMB, and to resolve issues raised by the trial coordinating centers.

[name], as coordinating investigator, is responsible for the governance of the study with the Scientific Committee, the Study Sponsor, and the DSMB.

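### Serious adverse events are defined by intensity grade alone, while the reporting rule treats serious and severe events as separate items; the two passages must be reconciled

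*Protocol article*

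**What the plan says.** Study endpoints ends with the safety data. It first says, with no limit on grade, that the proportion of adverse events will be compared between the groups. It then defines the serious ones: "All expected and unexpected serious adverse events, as defined as EMA grade 3 (severe), 4 (life-threatening), to 5 (lethal"). These "will be systemically recorded on day 1 and day 7", and the definition feeds a result: "The proportion of expected and unexpected serious adverse events will be analyzed and reported in future publications".

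Study oversight sets the reporting route: "Serious adverse events and unexpected related or possibly related severe events are reported to the sponsor within 7 days". It offers no definition of its own and does not refer back to the grades. The data and safety monitoring board (DSMB) is given a broader remit: "Every 400 inclusions, the DSMB reviews safety issues as the study progresses". Its ground for recommending permanent termination is again worded by severity.

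The Discussion paragraph of the abstract says the trial "will be carried out according to the principles of the Declaration of Helsinki and the Good Clinical Practice guidelines".

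**The concern.** Seriousness and severity answer different questions. Severity is how intense an event was. Seriousness is what it led to: death, threat to life, new or prolonged hospitalisation, lasting disability, or something else medically important. Safety reporting in trials run to Good Clinical Practice ordinarily keeps the two as separate attributes of each event. The definition in Study endpoints merges them.

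Two uses depend on the definition. One is the SAE proportion to be analysed and published. If it is built on grade, it does not measure what readers will take it to measure and cannot readily be set beside SAE rates from other trials. The other is the report to the sponsor. A site reading the two sections together cannot tell whether a low-grade event that prolonged the stay must be reported, or why severe events are listed separately.

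**Working it through.** No arithmetic applies. The check is a reading of every statement on adverse events, grades and safety reporting, followed by a comparison of two rules.

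**1. Is an outcome criterion given anywhere?** The sections read were Study endpoints, Study oversight and the analysis of secondary endpoints. None mentions hospitalisation, prolonged stay, disability or medical importance as a test of seriousness. The grade rule is the only definition in the article, and it is worded as a definition rather than as an example.

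**2. How does the grade rule compare with an outcome rule?**

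| Event | Grade rule as written | Outcome rule | Agree? |
|---|---|---|---|
| Grade 1–2, no serious outcome | not an SAE | not an SAE | yes |
| Grade 1–2, prolonged stay or lasting disability | not an SAE | SAE | **no** |
| Grade 3, no serious outcome | SAE | not an SAE | **no** |
| Grade 3, serious outcome | SAE | SAE | yes |
| Grade 4 (life-threatening) | SAE | SAE | yes |
| Grade 5 (lethal) | SAE | SAE | yes |

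Disagreement is confined to grades 1 to 3 and runs in both directions, so the net effect on the SAE proportion has no predictable sign.

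**3. Do the two sections fit together?** Suppose *serious* means grade 3 or above. Then every severe event is already serious, and the second item in the Study oversight sentence (unexpected, related or possibly related severe events) adds nothing. Suppose instead that *serious* is judged by outcome. Then the second item adds severe events with no serious outcome, and the sentence is coherent, but it conflicts with Study endpoints. Either one item is redundant or the two sections use the word differently.

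**4. What is still captured by another route?**
- Pulmonary aspiration, desaturation and severe anaphylaxis in the first 10 minutes belong to the primary composite.
- In the recovery room, aspiration, laryngeal dyspnoea, low oxygen saturation and respiratory support after extubation are secondary endpoints, as are "proportion of reintubation, and proportion of postoperative emergency ICU admission".
- Pneumonia, acute respiratory failure and death to day 7 are secondary endpoints.
- The between-group comparison of adverse events has no grade restriction.

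None of these depends on the SAE definition. Prolonged hospitalisation and persistent disability are not listed as endpoints, so a grade 1–2 event with only such an outcome has no stated route into the SAE record.

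**5. How many events?** A count would need the rate of events serious by outcome and the share of them graded 1–2, plus the rate of grade 3 events without serious outcome. The document gives none of these, so no number is offered.

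**The case against.** The strongest reply has four parts.

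First, the events that matter most to this trial are collected anyway. This stands. A reader might infer that moderate respiratory and airway events vanish, and that the research question on postoperative respiratory complications is compromised. The document does not support that: the question is answered by named endpoints, and lower-grade events remain in the overall adverse event comparison. What is lost is their place in the SAE proportion and possibly in the sponsor report.

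Second, Study oversight does not cite the grade rule and may keep the two concepts apart. This also stands. A reader might conclude that sponsor alerts are definitely wrong. The text supports only a conditional statement: they are affected if that section uses the one definition given. The DSMB reviews safety issues generally, so its view is not shown to be confined to grades 3 to 5. But the reply concedes that the two sections then use the term differently, which is the inconsistency itself.

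Third, the article condenses a longer protocol that may define SAEs conventionally, and sites work from that protocol and the case report form. This limits what can be said about site practice. It does not excuse the sentence, which states a definition rather than leaving one out.

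Fourth, the grading scale is not reproduced. One cannot show from the document that an aspiration leading to intensive care could be graded 2, or that an inconsequential sore throat could be graded 3. Such examples should not be relied on. If the full text of the scale brings hospitalisation into grade 3, the omission of serious events shrinks; the mismatch between the sections would still need clarifying.

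**Conclusion.** The point holds as a definitional error with an internal inconsistency. Study endpoints makes intensity the sole test of seriousness, and Study oversight uses *serious* and *severe* as separate terms. As written, the published SAE proportion would omit grade 1–2 events that prolong hospitalisation or cause lasting disability and would include grade 3 events with no serious outcome. Whether the 7-day report shares the problem depends on whether it relies on the same definition.

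The consequence is moderate and lies in safety reporting only. Life-threatening and lethal events are classified correctly. The primary endpoint, non-inferiority margin and sample size are unaffected. The conclusion assumes that grades 1 to 3 are pure intensity grades, as the label for grade 3 suggests, and that no unseen text overrides the definition.

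**What to change.** In Study endpoints, define an SAE by outcome: death, threat to life, new or prolonged hospitalisation, persistent disability, or another medically important event. Record the intensity grade for each event in its own field. Use the same definition in Study oversight and in the between-group SAE comparison, and state there whether severe but non-serious events are a separate reporting category. If the full protocol already defines SAEs this way, correct the published text to match.

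For patients already enrolled (340 by the March 2020 suspension, more since), reclassify from the collected data where possible, so that the SAE proportion does not rest on two definitions. Emergency intensive care admission, reintubation and death are already recorded; prolonged stay and disability would need a return to the medical record, so reclassification may be incomplete.

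The cost is some additional SAE forms, the re-review of earlier records, and a protocol amendment. If the amendment counts as substantial, it goes to the regulator and the ethics committee under the Protocol amendments section.

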### Schedule of enrolment, interventions, and assessments

A schematic diagram of the REMICRUSH study is available in Supplemental Figure S2. No biological specimens would be collected as part of this trial.

### Follow-up data

Most of the data are collected during the first 10 min after induction of anesthesia. As the anesthetic procedure progresses, the data collection sheet is completed in the recovery room and attached to the medical record. Data are also reported in a centralized electronic case report form. The duration of patient follow-up is 7 days. In the event of earlier discharge from the hospital, patients are considered free from complications for the days out of the hospital.

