### Research questions

Is remifentanil, in association with a hypnotic, non-inferior to rapid-onset paralytic agents considering successful tracheal intubation without major complications?Does remifentanil use in rapid sequence induction allow similar conditions for tracheal intubation in patients at risk of pulmonary aspiration of gastric contents than rapid-onset paralytic agents?Does remifentanil use in rapid sequence induction reduce the risk of postoperative respiratory complications?

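### Days after discharge are scored as complication-free, so pneumonia and respiratory failure up to day 7 are in effect in-hospital endpoints; the pneumonia leukocyte limits also carry the wrong unit

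*Protocol article*

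**What the plan says.** Follow-up data in the protocol article fixes the horizon, "The duration of patient follow-up is 7 days", and then gives a scoring rule for patients who leave earlier: "In the event of earlier discharge from the hospital, patients are considered free from complications for the days out of the hospital".

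Study endpoints, in the part on the period after the recovery room, lists:
- "percentage of patients with postoperative pneumonia diagnosed up to day 7";
- "percentage of patients with acute respiratory failure occurring up to day 7";
- "intra-hospital mortality up to day 7, and survival proportion at day 7".

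The same section says that serious adverse events of grades 3 to 5 "will be systemically recorded on day 1 and day 7". Research questions includes: "Does remifentanil use in rapid sequence induction reduce the risk of postoperative respiratory complications". The secondary-endpoint paragraph under Pre-planned primary analysis assigns logistic regression to postoperative pneumonia and respiratory distress.

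The pneumonia definition requires a new or progressive infiltrate plus any one item from a list. One of those items reads "hyperleukocytosis (> 12,000/mL) or leukopenia (< 4000/mL".

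**The concern.** The rule is a positive instruction, not a detail left for a fuller document. It gives every unobserved day after discharge the favourable value. The endpoint names promise a risk over seven days, but a patient who leaves on day 2 contributes two days of observation and five days of assumption. A pneumonia that appears at home on day 5 counts as no event.

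The rule also sits uneasily with the day-7 recording of serious adverse events. If discharged patients are checked on day 7, the rule could override known information. If they are not checked, the day-7 safety record is incomplete for them. The article does not say which holds.

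At stake is the reading of part of the third research question. Few recorded events, or a small absolute difference, could reflect when patients left hospital and not how they fared. The leukocyte unit is a separate slip in the same endpoint definition.

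**Working it through.** **Inputs from the article.** 575 patients per group, 1:1 (Sample size; Treatment allocation), and logistic regression for the two respiratory endpoints. The rule has no figure of its own. The group size used below does reproduce, with 80% versus 73%, one-sided 2.5% and 80% power:

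n = [1.96·√(2·0.765·0.235) + 0.8416·√(0.80·0.20 + 0.73·0.27)]² / 0.07² = 574.8, rounded up to 575 per group (1150 in total).

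**Assumed inputs.** The article gives no day-7 event rates and no lengths of stay. Let p be the true 7-day risk in an arm and s the share of true events that fall on in-hospital days. Assume no false positives. The rule then records a risk of s·p.

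**Equal capture in both arms.**
- Risk difference: s·(p₀ − p₁), which shrinks in proportion to s.
- Risk ratio: s·p₁ / (s·p₀) = p₁/p₀, unchanged.
- Odds ratio: [s·p₁/(1 − s·p₁)] / [s·p₀/(1 − s·p₀)], almost unchanged when risks are small.
- Power: two-sided 5% comparison of two proportions, pooled variance under the null, 575 per group.

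With p₀ = 4% (control) and p₁ = 2% (remifentanil):

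| s | Recorded risks | Difference (points) | Risk ratio | Odds ratio | Power |
|---|---|---|---|---|---|
| 1.0 | 4.0% vs 2.0% | 2.0 | 0.50 | 0.490 | 51% |
| 0.8 | 3.2% vs 1.6% | 1.6 | 0.50 | 0.492 | 43% |
| 0.6 | 2.4% vs 1.2% | 1.2 | 0.50 | 0.494 | 33% |
| 0.4 | 1.6% vs 0.8% | 0.8 | 0.50 | 0.496 | 24% |

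At s = 0.6 the odds ratio is (0.012/0.988)/(0.024/0.976) = 0.494. Across assumed true risks from 2% versus 1% up to 10% versus 6%, power runs from 29% to 71% with full capture and from 14% to 34% at s = 0.4. The odds ratio moves by at most 0.016 (0.574 to 0.590, at 10% versus 6%).

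**Unequal capture.** Take equal true risks of 4%, so there is no effect.
- s = 0.8 in control and 0.6 in remifentanil: recorded risks 3.2% versus 2.4%, odds ratio (0.024/0.976)/(0.032/0.968) = 0.74.
- The reverse: odds ratio 1.34.

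The direction follows whichever arm goes home sooner, or has more of its events after discharge.

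**Leukocyte unit.** 1 mL is 1000 mm³, so the printed limits equal 12 and 4 cells per mm³. Normal counts are in the thousands per mm³, that is, millions per mL. Read literally, nearly every patient exceeds the upper limit. Since one listed item is enough, the definition collapses to a new or progressive infiltrate.

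**The case against.** The strongest reply is that these are secondary endpoints and that little is biased on the planned scale. That largely stands. A reader might infer that the rule biases the respiratory comparison towards no difference. With equal capture this holds for the risk difference, but not for the risk ratio and not materially for the odds ratio, which is the scale of the planned logistic model. With unequal capture the direction is open. The Introduction's remark that rocuronium block can outlast surgery does not settle it: nothing in the article links that to the day of hospital discharge, and controls may receive succinylcholine instead.

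Three further stronger readings are not supported:
- *Day-7 survival is simply one minus in-hospital mortality.* The rule speaks of complications and does not name death, survival is listed separately, and lethal events belong to the day-7 safety record. What remains is that the article does not show where vital status after discharge comes from.
- *The whole third research question is compromised.* Desaturation, laryngeal dyspnea, respiratory support and reintubation are observed in the recovery room, and in-hospital events up to day 7 still count.
- *The rule flatly contradicts the day-7 safety recording.* A scoring convention and a safety record can coexist; the text needs reconciling.

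It is also fair that coding every early discharge as missing is not clearly better. Missing values would concentrate in patients well enough to leave, and imaging or blood-gas criteria are often unobtainable at home. The safety record covers only grades 3 to 5, so it would miss milder pneumonia. As for the leukocyte limits, sites may well read them in the intended unit; the article does not show how the case report form prints them.

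**Conclusion.** The point holds in a limited form. As written, pneumonia and acute respiratory failure up to day 7 are in effect in-hospital endpoints, because days after discharge are declared event-free. Event counts, absolute risks, absolute differences and power are reduced. With equal capture by arm the odds ratio is nearly unaffected; if discharge timing or capture differs by arm, it can be biased either way.

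The actual size cannot be stated from the article. The figures above rest on assumed risks and assumed capture, and on an unadjusted comparison without the planned stratification and centre terms. The 10-minute primary endpoint, the sample size of 1150 and the recovery-room respiratory endpoints are not affected.

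The leukocyte limits are wrong as printed by a factor of 1000, whatever view is taken of the discharge rule.

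**What to change.** Reconcile Follow-up data with Study endpoints:
1. Rename the two endpoints as in-hospital pneumonia and in-hospital acute respiratory failure, up to day 7, and limit the conclusion on the third research question accordingly.
2. Count any qualifying post-discharge event already captured in the day-7 safety record, instead of overriding it with no event.
3. Report time to discharge by arm, so that readers can judge whether capture was comparable. The discharge date is already needed to apply the present rule.
4. Report day-7 survival only where vital status on day 7 is actually known; otherwise drop it in favour of in-hospital mortality.
5. Separately, correct the leukocyte limits to more than 12,000 and fewer than 4,000 per mm³, and check that the case report form agrees.

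The cost is mainly wording, one descriptive table and a check of the safety record. No new patient contact is required, and neither the sample size nor the primary analysis changes. The downside is that the endpoints become narrower in-hospital outcomes and no longer support a statement about all respiratory complications within seven days.
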